*Relationship between general MPA level and challenge-threat*. Higher general MPA level is associated with greater increase in threat from the private to the public performance: With increasing general MPA level, change scores (public minus private) of the cardiovascular CTI and the resources-demands differential (self-rated resources minus self-rated demands) decrease.*Relationship between general MPA level and MPQ.* Higher general MPA level is associated with greater decrease in self-rated and expert-rated MPQ from the private to the public performance: With increasing general MPA level, change scores (public minus private) of self-rated and expert-rated MPQ decrease.*The mediating role of challenge-threat.* The cardiovascular CTI and the resources-demands differential are significant mediators of the relationships between general MPA level and self-rated and expert-rated MPQ.*Relationship between general MPA level and state anxiety.* Higher general MPA level is associated with greater increase in state anxiety from the private to the public performance: With increasing general MPA level, change scores (public minus private) of state anxiety increase.*Relationship between general MPA level and respiration.* Higher general MPA level is associated with greater increase in sigh rate and total respiratory variability and greater decrease in P_et_CO_2_: With increasing general MPA level, change scores (public minus private) of sigh rate and total respiratory variability increase, whereas change scores of P_et_CO_2_ decrease.*Relationship between general MPA level and salivary measures of HPA axis activity and SAM axis activity.* Higher general MPA level is associated with greater increase in sC and greater decrease in sDHEA, anabolic balance and sAA: With increasing general MPA level, change scores (public minus private) of sC increase, whereas change scores of sDHEA, anabolic balance and sAA decrease.

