### Final online questionnaire

One week after completing the second performance session, participants will receive the recordings of their two performances via an e-mail containing a link to a final online questionnaire and a Dropbox link to two mp3 audio files named “Recording1” for the first performance session and “Recording2” for the second performance session. In the online questionnaire, participants will be asked to listen to these audio files in the same order and rate the MPQ using the MPQ Scale.

Finally, the participant will fill in questionnaires assessing their trait anxiety, social anxiety and depressive symptoms, all of which are potential confounding variables because they can affect the psychophysiological measures.

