#### Practice time

The amount of practice time for each session performance is a secondary measure assessed at the end of each performance session (Q6) with the question “How much time have you spent in the last 48 hours specifically preparing the musical piece you have just played?”. Participants will respond by indicating a numerical value.

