### Data-analytic strategy

Scores for self-report measures will be computed in accordance with guidelines. For cardiovascular and respiratory measures, scores will be computed for the 8-min sitting period, the 4-min performance period, and the three 5-min post-performance sitting periods, with focus on the 8-min sitting period, as this is the most relevant period with regard to our hypotheses. The area under the curve with respect to ground and to increase will be calculated for the salivary parameters [81].

Given the repeated measures design, we will use multilevel mixed-effects modeling following state of the art procedures [82, 83]. For the mediation analyses, we will follow the model suggested by Baron and Kenny [84]. The main predictors are performance session (private vs. public), general MPA level and their interaction. Where appropriate, skewed variables will be transformed. We will use an alpha level of 0.05 for all tests. We will perform sensitivity analyses adding control variables to the models if they are theoretically meaningful and significantly related to the outcome variable. Potential control variables are age, gender, use of hormonal contraceptives, menstrual cycle phase, BMI, smoking, trait anxiety, social anxiety, depressive symptoms, academic year, practice time, session order, and motion.

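### Person-level control variables added without a session interaction leave the MPA × session estimate unchanged, so most of the planned sensitivity analyses would say nothing about confounding of the moderation hypotheses

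*Protocol article*

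**What the plan says.** The hypotheses at the end of the Background section are worded as changes. Set 1 expects that, as MPA rises, "change scores (public minus private) of the cardiovascular CTI and the resources-demands differential (self-rated resources minus self-rated demands) decrease". Set 4 reads: "With increasing general MPA level, change scores (public minus private) of state anxiety increase". Sets 2, 5 and 6 have the same form.

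Under Data-analytic strategy the model class is given ("we will use multilevel mixed-effects modeling following state of the art procedures"), followed by its terms: "The main predictors are performance session (private vs. public), general MPA level and their interaction". The change hypotheses are therefore tested through MPA × session.

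The same section gives the rule for controls: "We will perform sensitivity analyses adding control variables to the models if they are theoretically meaningful and significantly related to the outcome variable". There are 13 candidates: age, gender, hormonal contraceptives, menstrual cycle phase, BMI, smoking, and then "trait anxiety, social anxiety, depressive symptoms, academic year, practice time, session order, and motion". No interaction of a control with session is mentioned.

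The Final online questionnaire section explains why trait anxiety, social anxiety and depressive symptoms are collected: "all of which are potential confounding variables because they can affect the psychophysiological measures". Each is measured once.

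**The concern.** General MPA level is observed, not randomised. If students with high MPA also have higher trait anxiety, and trait anxiety drives the reaction to an audience, MPA × session will pick that up. The sensitivity analyses are the stated check on such explanations.

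A control with one value per person, added as a main effect, shifts both of that person's sessions equally. It can change the MPA main effect but not the within-person contrast that carries the hypotheses. The report could then say that results were unchanged after adjustment for trait anxiety, social anxiety and depression, when the algebra allowed no other result.

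**Working it through.** The plan states no figure for this check, so there is none to reproduce. The steps below classify the controls, show the cancellation, and illustrate its consequence.

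**1. Inputs from the article**
- 100 participants with complete data (Participants; Possible challenges), hence complete pairs.
- Two sessions, 2 days apart, in randomised order (Private and public performance sessions).
- Alpha 0.05 (Data-analytic strategy), taken here as two-sided.

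**2. Which controls vary within a person**
- One value per person: age, gender, contraceptive use, BMI, smoking, trait anxiety, social anxiety, depressive symptoms, academic year, session order. Menstrual phase is effectively constant over 2 days. Total 11.
- Varying by session: practice time (asked at each performance session) and motion (recorded by the respiratory device worn in each session). Total 2.

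**3. Algebra.** Let Z be a person-level control entered as a main effect and u the person's random intercept:
- private: y = a1 + b1·MPA + c·Z + u + e1
- public: y = a2 + b2·MPA + c·Z + u + e2
- difference: (a2 − a1) + (b2 − b1)·MPA + (e2 − e1)

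Z has gone. With complete pairs the estimate of b2 − b1 is the same with or without Z.

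**4. Simulation** (random-intercept REML, 100 people, two sessions). Assumptions, not from the article: trait anxiety correlates 0.6 with MPA and acts on the change with slope -0.4; MPA raises practice time in the public session by 0.5 per unit; practice time acts on the outcome with slope 0.3; MPA has no other effect on the change. Expected MPA × session values:
- no adjustment: 0.3 × 0.5 + 0.6 × (-0.4) = 0.15 − 0.24 = -0.09
- trait anxiety × session added: +0.15
- practice time added: -0.24

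| Model | Mean over 100 data sets | Largest shift from base | One data set (SE) |
|---|---|---|---|
| Base | -0.083 | – | -0.187442 (0.1214) |
| + trait anxiety, age, order as main effects | -0.083 | 0.000000 | -0.187442 (0.1214) |
| + trait anxiety × session | +0.149 | 0.44 | +0.103 (0.1465) |
| + practice time (session-level) | -0.244 | 0.29 | -0.312 (0.1262) |
| + order × session | -0.082 | 0.044 | -0.164 (0.1226) |

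In the single data set, the main-effect adjustment moved only the MPA main effect, from 0.476 to 0.248. With 13 public sessions deleted, it moved the interaction only from -0.2378 to -0.2401.

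**5. The screening rule.** In this simulation trait anxiety has slope 0.5 on the private outcome and 0.5 − 0.4 = 0.1 on the public one, an average of 0.3. It is related to the level and could pass the screen, yet as a main effect it does nothing to the interaction. Conversely, a change slope of -0.4 split as +0.2 (private) and -0.2 (public) averages zero. That control could be screened out although it acts on the change.

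**6. Illustrative false-positive rates.** If MPA has no effect, a confounder correlated r with MPA and ρ with the change induces an MPA–change correlation of r·ρ. At n = 100, by normal approximation:
- r = 0.3, ρ = 0.24: r·ρ = 0.072, shift 10 × 0.072 = 0.72, rejection rate P(Z > 1.24) + P(Z < -2.68) ≈ 0.11
- r = 0.6, ρ = 0.30: r·ρ = 0.18, shift 1.80, rejection rate ≈ P(Z > 0.16) ≈ 0.44

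Simulation over this range gave 11% to 45% with main-effect adjustment and about 5% with covariate × session. These r and ρ are assumptions.

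**The case against.** The strongest reply is that the article never says controls enter as main effects only. It does not exclude covariate × session terms, and a condensed article may leave functional form to a fuller plan. The hypotheses and the sample size model are also written in change scores. If the outcome variable means the change score, an added covariate adjusts the change directly and the screen is the right one.

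This stands in part: main-effect entry is the natural reading, not a stated rule. But the same paragraph specifies an interaction for the main predictors and none for the controls, and a model with session as a predictor has the session-level value as its outcome, not the change. An analyst following the text would most likely run the uninformative check.

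A reader might also infer that no listed control can move the estimate, so that every sensitivity analysis must come out unchanged. The documents do not support that. Practice time and motion vary by session and can shift the estimate as plain main effects, as practice time does in the table. Exact invariance also needs complete pairs.

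Nor can 11% to 45% be read as this study's error rate. The article gives no correlation of any confounder with MPA or with the change.

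**Conclusion.** The concern holds for the 11 person-level controls, including the three the article itself names as potential confounders. Entered without a session interaction, they leave the MPA × session estimate unchanged (shift 0.000000 with complete pairs), so an unchanged result is no evidence against confounding in hypothesis sets 1, 2, 4, 5 and 6. Judging relevance by relation to the outcome level does not repair this.

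The conclusion rests on main-effect entry as the natural reading, on complete pairs as planned, and on a random-intercept model with one score per session. It does not depend on the assumed correlations, which only illustrate possible consequences. The primary models are unaffected; the weakness is in the check on confounding.

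A reader might go further and want trait and social anxiety entered whatever their p-value. The documents do not support that as a clear improvement. General MPA is measured with the state scale of the same inventory whose trait scale measures trait anxiety, and the social anxiety scale includes 12 performance items. Adjustment may remove part of MPA itself, so attenuation would not by itself show confounding.

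**What to change.** Under Data-analytic strategy, state for the MPA × session hypotheses that:
- each person-level control in a sensitivity model enters together with its interaction with session, equivalently as a covariate in the regression of the change score on MPA;
- session order enters as order × session;
- relevance of a control is judged against the public-minus-private change, not the outcome level;
- practice time and motion stay as session-varying covariates;
- attenuation after adjusting for trait or social anxiety is interpreted cautiously, because these scales overlap with the MPA measure.

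The cost is wording, one extra degree of freedom per covariate, and wider intervals in the sensitivity analyses. In the data set tabulated above the standard error rose from 0.1214 to 0.1465 (0.1465 / 0.1214 = 1.21, or 21%). In a second simulated data set it rose from 0.0906 to 0.1163 (28%). No new data are needed.

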### Sample size calculation

The sample size calculation refers to the first three sets of hypotheses, which we consider to be the critical ones. The power computations are based on a model by which the effect of general MPA level on MPQ follows two paths, direct and indirect. In the indirect path, MPA acts on the cardiovascular CTI, which acts on MPQ. The computations rely on the repeated simulations of such a model. First, we fix the distributional parameters of MPA. We obtained a mean (*M*) of 45 on the STAI-S scale and a standard deviation (*SD)* of 12 [8]. We assume that general MPA level influences deltaCTI, i.e., the difference in CTI between private and public performance sessions. To simulate realistic values for deltaCTI, we rely on [85] who reported a difference in the cardiovascular CTI between a “challenge” group and a “threat” group of 0.9. Thus, we assume *M* = 0.9 for deltaCTI. Moore et al. [85] used a two-group design, while we use a repeated-measures design. To estimate *SD* of deltaCTI, we rely on [8] who used a similar design as in the planned project. In their study, *M* and *SD* of deltaHR between private and public sessions were 28 and 16, respectively. Assuming similar coefficients of variation for deltaHR and deltaCTI, we obtain *SD* = 0.9*16/28 = 0.5 for deltaCTI. From knowledge about distributions of general MPA level and deltaCTI and assuming normal distributions and linear relationships, we can deduce the equation of the linear regression from the following variance components: Var(deltaCTI) = variance of deltaCTI, Var_Res_ = residual variance, Var(MPA) = variance of MPA. The slope beta_deltaCTI_MPA_ is the square root of (Var(deltaCTI) – Var_Res_)/Var(MPA), and the intercept is mean(deltaCTI) - beta_deltaCTI_MPA_*mean(MPA). Defining the effect size using Cohen’s [86] η^2^, where η^2^ = (Var(deltaCTI)-VarRes)/ Var(deltaCTI), the model relating MPA and deltaCTI is specified. Next, we specify the effect of deltaCTI on deltaMPQ, where deltaMPQ is the difference in MPQ between public and private performance sessions. We assume a linear relationship with slope beta_deltaMPQ_deltaCTI_. Without any loss of generality, we can specify the linear relation without intercept and with residual *SD* = 1. Thus, the indirect effect of MPA on deltaMPQ is beta_indir_ = beta_deltaCTI_MPA_*beta_deltaMPQ_deltaCTI._ Next, we assume that there is also a direct effect given by the slope beta_dir_, which is determined by the assumed mediated proportion (MP): beta_dir_ = beta_deltaCTI_MPA_*beta_deltaMPQ_deltaCTI_*(1-MP)/MP. In summary, given a simulation of MPA, we simulate deltaCTI and deltaMPQ = beta_deltaMPQ_deltaCTI_ *deltaCTI + beta_dir_*MPA + e, e ~ N(0,1). Finally, we define that small-to-medium effects (according to [86] criteria for interpreting η^2^) of MPA on deltaMPQ, MPA on deltaCTI and deltaCTI on deltaMPQ and MP between 20 and 30% are scientifically meaningful. By running 10′000 simulations of the aforementioned model with different combinations of the parameters, we determine that these effects are significant at α = 0.05 and power > 0.80 with a sample of 100 participants.

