## Methods/design

### Participants

Participants will be university music students recruited from university music schools by means of electronic invitations and posting on social media. Based on sample size estimations (see chapter Sample size calculation), we aim to collect complete data from 100 students.

Participants will have to be students in the department of classical music, between 18 and 35 years of age and in general good health. Exclusion criteria are cardiovascular, neurologic, respiratory and endocrine diseases, and the use of drugs with effects on the cardiovascular, nervous, respiratory and endocrine systems, including recreational drugs, beta-blockers and anxiolytic medication. Individuals wearing a pacemaker and working night shifts will also be excluded. A current diagnosis of panic disorder or eating disorders are additional exclusion criteria. Women will be excluded if they are pregnant or lactating. Eligibility to participate will be determined with an entry online questionnaire. Participants will receive 250 Swiss Francs as compensation if they complete all phases of the study protocol.

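### Power above 0.80 with 100 participants is claimed without effect sizes or sidedness; common two-sided benchmarks do not reach it, and mediation power is lower and not reported

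*Protocol article*

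**What the plan says.** The protocol article, under Sample size calculation, sets the scope: "The sample size calculation refers to the first three sets of hypotheses, which we consider to be the critical ones". The third of these sets is the mediation hypothesis.

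The section then describes a simulation model. General MPA level acts on deltaCTI, deltaCTI acts on deltaMPQ, and a direct MPA effect is fixed by the mediated proportion. The effects to be detected are small-to-medium by a cited eta-squared criterion, namely "MPA on deltaMPQ, MPA on deltaCTI and deltaCTI on deltaMPQ and MP between 20 and 30% are scientifically meaningful". The conclusion is that "we determine that these effects are significant at α = 0.05 and power > 0.80 with a sample of 100 participants".

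Under Participants, the target follows from this: "we aim to collect complete data from 100 students". Under Data-analytic strategy, the article states "We will use an alpha level of 0.05 for all tests" and names the Baron-Kenny model for mediation. No section gives a numerical eta-squared, says whether tests are one- or two-sided, or gives a separate power for the mediation test.

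**The concern.** The power sentence is the only justification for 100 participants, and it is worded to cover every small-to-medium effect in the three hypothesis sets. Two things look wrong.

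- A single regression slope with n = 100 does not have 80% power for effects commonly called small-to-medium, unless the test is one-sided and the effect lies at the top of that range.
- A mediation claim under Baron-Kenny needs several tests to be significant together. Its power can be no higher than that of the weakest test, yet the article lets one figure stand for all.

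What is at stake is the reading of a null result. The Discussion says the findings will show how far the challenge-threat framework is valid for music performance. If mediation is non-significant, a reader who trusts the stated power will count that as evidence against the mechanism.

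**Working it through.** **Inputs from the protocol article**

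- n = 100 with complete data; alpha 0.05.
- MPA: "We obtained a mean (*M*) of 45 on the STAI-S scale and a standard deviation (*SD)* of 12".
- deltaCTI: mean 0.9, and "we obtain *SD* = 0.9*16/28 = 0.5 for deltaCTI". The product is 0.514, given rounded.
- deltaMPQ = b × deltaCTI + direct × MPA + error, with error SD 1 and direct = a × b × (1 − MP)/MP. Here a is the slope of deltaCTI on MPA.
- MP 20-30%.

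**Assumptions.** Eta-squared 0.01 to 0.06, with 0.13 shown as a wider reading. Two-sided tests as the base case and one-sided as a variant. In the mediation cells, a and c (total effect of MPA on deltaMPQ) have equal eta-squared.

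**Reproducing the stated figure.** No single value can be recomputed, because eta-squared and sidedness are missing. The means and SDs do not help: once eta-squared and MP are fixed, the slope tests do not depend on location or scale.

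**Step 1: one path.** Noncentrality = √(n × η²/(1 − η²)), with 98 degrees of freedom and critical t 1.984 two-sided or 1.661 one-sided.

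- η² = 0.01: √(100 × 0.01/0.99) = 1.01
- η² = 0.06: √(100 × 0.06/0.94) = 2.53
- η² = 0.074: √(100 × 0.074/0.926) = 2.83

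| η² | Power, two-sided | Power, one-sided |
|---|---|---|
| 0.01 | 0.17 | 0.26 |
| 0.035 | 0.47 | 0.60 |
| 0.06 | 0.71 (0.70 simulated) | 0.81 (0.80 simulated) |
| 0.074 | 0.80 | 0.88 |
| 0.13 | 0.97 | 0.99 |

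Solving for power 0.80 gives η² = 0.074 two-sided and 0.059 one-sided. These figures apply to MPA on deltaCTI and to MPA on deltaMPQ.

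**Step 2: what MP implies for the mediator path.** The total effect is c = ab + ab(1 − MP)/MP = ab/MP. In standardised units, a = c therefore gives b = MP. The partial eta-squared of deltaCTI given MPA is b²(1 − a²)/(1 − c²), which equals MP² when a = c. That is 0.04 at MP 20%, 0.0625 at 25% and 0.09 at 30%, however large a and c are. Simulated power of this adjusted path is 0.51, 0.71 and 0.86 two-sided. At MP 20% one-sided it is about 0.63.

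**Step 3: mediation.** The model was simulated with at least 10,000 runs per cell and n = 100. Repeat runs differ by about 0.01.

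| a = c | MP | a and b, two-sided | three steps, two-sided | a and b, one-sided | three steps, one-sided |
|---|---|---|---|---|---|
| 0.0588 | 20% | 0.35 | 0.25 | 0.49-0.50 | 0.39-0.40 |
| 0.0588 | 25% | 0.49 | 0.36 | 0.64 | 0.52 |
| 0.0588 | 30% | 0.59 | 0.44 | 0.72 | 0.60 |
| 0.13 | 20% | 0.50 | 0.48 | 0.63 | 0.62 |
| 0.13 | 25% | 0.68 | 0.66 | 0.79 | 0.78 |
| 0.13 | 30% | 0.83 | 0.80 | 0.90 | 0.89 |

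In the table, b is the adjusted deltaCTI path, and the three steps are a, b and c all significant. At exactly 0.06 the entries are at most about 0.02 higher.

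**Step 4: a bound without the equal-effects assumption.** Joint power cannot exceed the power of path a. If MPA explains at most 6% of deltaCTI, two-sided mediation power is at most about 0.70, whatever b is.

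**The case against.** The strongest reply is that the authors gave no eta-squared number, so the range 0.01 to 0.06 is mine. The source they cite for the criterion is not available here. The hypotheses are directional, and one-sided at 0.06 the paths MPA on deltaCTI and MPA on deltaMPQ do reach about 0.80. Two-sided, they reach it from 0.074. The simulation also ran different parameter combinations, so nothing in the article forces a and c to be equal. Nor does it say whether the deltaCTI effect is adjusted for MPA. Unadjusted, at a = c = 0.06, its two-sided power is 0.70 to 0.94 across MP 20-30%. Finally, a journal article may leave the simulation grid to the full protocol.

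Most of this stands, and it rules out several stronger readings that a reader might infer:

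- **That the power figure is an arithmetical error.** The document leaves too much unstated to show that; some readings reach 0.80 for single paths.
- **That mediation power is always below one half, or reaches 0.80 only if both component paths have eta-squared near 0.10.** Neither is general. With a = c = 0.0588 and MP 30%, joint power is 0.59. With a = c = 0.13 and MP 30%, where the adjusted mediator path has 0.09, it is 0.83.
- **That the adjusted deltaCTI path can never reach 0.80.** At MP 30% with a = c it has 0.86 two-sided.

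What the reply does not answer is the breadth of the claim. The low end of the assumed range fails under either sidedness (0.17 or 0.26 at 0.01). An unadjusted deltaCTI association is not the Baron-Kenny mediator test. At MP 20%, inside the authors' own range, the adjusted path stays near 0.51 two-sided or 0.63 one-sided when a and c are equal, even at 0.13. The objection is to a definite statement in the article and does not depend on omitted detail.

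**Conclusion.** The point holds in a limited form. The claim of power above 0.80 cannot be verified without the eta-squared values and sidedness. Assuming eta-squared 0.01 to 0.06 and two-sided tests, it is not met for MPA on deltaCTI or MPA on deltaMPQ (0.17 to about 0.70).

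As a blanket figure that includes mediation, it is not delivered under either sidedness. With a and c at about 0.06 and MP 20-30%, power for a and b jointly is 0.35-0.59 two-sided and 0.49-0.72 one-sided. For all three Baron-Kenny steps it is 0.25-0.44 and 0.39-0.60.

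The mediation ranges rest on equal a and c, which is my assumption. The conclusion that mediation power is no higher than that of the weakest path does not depend on it. Nothing here shows that 100 participants is the wrong number; the defect lies in what that number is said to deliver.

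**What to change.** Keep n = 100 and revise the sample size section as follows.

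1. State the eta-squared values, the MP values and the sidedness used in the simulations, and whether the deltaCTI effect is adjusted for MPA.
2. Restate the single-path claim, for example: *with 100 participants and two-sided alpha 0.05, power is 0.80 for a single path at eta-squared of at least 0.074.*
3. Report power for the mediation test separately, taken from the authors' own simulation, under the Baron-Kenny criterion that will be applied and across MP 20-30%.
4. Describe hypothesis set 3 as limited in power, and say that a non-significant mediation result will not be read as evidence against the mechanism.

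This costs rewording and the tabulation of mediation power from the existing simulation model. No extra participants are needed. The downside is that the stated power becomes less favourable.
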